#### Up to 600 stings

Without anaphylactic shock:➢ catheterize a central vein for hydration of the patient;➢ follow the protocol contained in the symptomatic treatment item;➢ remove all the stingers correctly;➢ these individuals must always be hospitalized in an ICU;➢ apply six vials of apilic antivenom.
In the presence of anaphylactic shock:➢ catheterize a central vein for hydration of the patient;➢ follow the protocol contained in the symptomatic treatment item;➢ remove all the stingers correctly;➢ these individuals may need to be hospitalized in an ICU;➢ apply six vials of apilic antivenom.

#### More than 600 stings

Without anaphylactic shock:➢ catheterize a central vein for hydration of the patient;➢ follow the protocol contained in the symptomatic treatment item;➢ remove all the stingers correctly;➢ these sick individuals in general require hospitalization in an ICU;➢ apply ten vials of apilic antivenom.
In the presence of anaphylactic shock:➢ catheterize a central vein for hydration of the patient;➢ follow the protocol contained in the symptomatic treatment item;➢ remove all the stingers correctly;➢ these sick individuals in general require hospitalization in an ICU;➢ apply ten vials of apilic antivenom.

### Clinical parameters

Product safety will also be evaluated through the clinical parameters verified in the evaluations, via both laboratory exams and adverse events that will have occurred during the study.

#### Adverse event (AE)

According to the International Council for Harmonisation of Technical Requirements for Pharmaceuticals for Human Use (ICH) [15], an adverse event is any undesirable clinical occurrence in a patient or participant in clinical research that receives or utilizes a pharmaceutical product and that does not necessarily present a causal relation to this treatment. Thus, an adverse event can be any unfavorable unintentional signal (including an abnormal laboratory finding, symptom or disease temporally associated with the use of a product under investigation, considered related or not to it). Preexisting conditions that worsen during a study must be reported as an AE. The events observed during a clinical study should be reported in the patient’s chart (source document), on the page of events of the electronic clinical registry and must be classified as to:Intensity➢ minimal (degree I): discomfort perceived, but without interruption of normal daily activity;➢ moderate (degree II): discomfort sufficient to reduce or inhibit daily activity;➢ severe (degree III): incapacity to work or perform normal daily activity;➢ risk to life (degree IV): represents an immediate risk to life;➢ death (degree V).
Causal relation➢ **probable**: the temporal relation is well defined without the existence of another possible causal factor. In this case, there is an almost certain relationship between the reaction and the medicament;➢ **possible**: a temporal relation between an event and the administration of a medicament is well defined, but there is another possible causal factor;➢ **remote**: a relationship with the medicament is improbable, but cannot be definitively discarded;
**➢ not related**: a temporal relationship between an event and the ingestion or administration of a medicament is nonexistent or doubtful, or there exists another factor that may be identified as a causal factor of the reaction.

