### Design of the *Apis* study

This is a multicenter, non-randomized and open phase I/II clinical trial study to evaluate the safety, determine the pharmacokinetic and proteomic profile, and confirm the lowest antivenom dose, according to the severity of each case. It will include 20 adult individuals, of both sexes, afflicted with multiple stings from Africanized *Apis mellifera* honeybees. The study population will be of the type non-probabilistic by convenience (or accidental) sample, given the low demographic density of the studied phenomenon and the extreme geographic decentralization of this event. The sample size was estimated by considering examples of phase I/II clinical studies proposing to study the safety and neutralizing power and to confirm the minimum required dose of antivenom [12]. Not performing the sample calculation is justified by the fact that the efficacy outcome is not the target at this moment given that there are no data on safety and adequate dose. The study will last 36 months, with 24 months for recruitment.

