### Objectives

Primary objectives: to evaluate the safety of the antivenom including number and severity of acute adverse events, as well as deaths suspected to be related to the intervention; and to confirm the lowest effective dose when faced with different quantities of venom inoculated in patients exposed to multiple stings from Africanized honeybees.Secondary objectives: to correlate the severity of the initial clinical condition with number of stings.Explanatory objectives: to evaluate the antivenom neutralizing power by pharmacokinetic and proteomic studies; and to evaluate the antivenom pharmacokinetics and immunogenicity.

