### Outcomes

Primary outcomes: to evaluate the antivenom safety profile through laboratory and clinical adverse events; to verify the proportion of individuals with improvement in the initial clinical picture by monitoring signs, symptoms and laboratory exams.Secondary outcomes: to evaluate the degree de correlation between the number of stings and the severity of the initial clinical picture (APACHE II).Exploratory outcomes: to evaluate the pharmacokinetic and immunogenic profile of antivenom/venom at doses established by an analysis of the blood samples collected at different moments (before and at 2, 6, 12 and 24 h after heterologous serum therapy); to evaluate the proteomic profile of the antivenom as determined by the differential expression of the proteins albumin, C-reactive protein (CRP) and fibrinogen, by the presence of the components melittin and phospholipase A_2_, and by the heterologous serum protein profile of the degradome and peptide/protein biomarkers.

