#### Symptomatic treatment

At the discretion of the medical team, goals for the patient include:To treat and prevent hypersensitivity reactions inherent to venom or antivenom. For this, use:➢ antihistamines – inject intramuscularly, one vial of 50 mg of promethazine or similar option upon the arrival of the patient; repeat every six hours if necessary;➢ corticosteroids – administer intravenously, 200 mg of hydrocortisone or similar option upon the patient’s arrival; repeat every six hours if necessary. This scheme could be maintained for 3 to 5 days, according to the clinical evolution;➢ when anaphylactic shock is suspected – if the patient presents severe hypotension and in the absence of a palpable pulse, inject subcutaneously 500 μg (0.5 mL) of aqueous adrenaline 1:1,000.
Treat the pain: inject intramuscularly, one vial of petidine chlorhydrate 50 mg or similar; repeat every six hours if necessary.In the presence of bronchospasm: utilize a catheter of oxygen (O_2_) associated with bronchodilators of the type β-2-agonist inhalants (salbutamol, phenoterol or terbutaline), at customary doses used at the referring center. Continue as needed until the disappearance of symptoms.

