#### Serious adverse event (SAE)

A serious adverse event is an AE that occurs during any phase of the study and that meets the following criteria: it threatens life; it results in death or a significant or permanent incapacity, congenital anomaly, hospitalization or the prolongation of an existent condition.

Serious adverse events also should be classified according to the guidelines of the previous item, filled out in the SAE formulary, sent to the coordinating center within 24 h of obtaining the knowledge by means of a virtual study platform and should be reported concomitantly with the system CEP-CONEP. The coordinating center will immediately notify ANVISA and subsequently the Department of Science and Technology in the Ministry of Health (DECIT/SCTIE/MS).

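### The causality categories *possible* and *not related* overlap, so most acute reactions, and deaths with venom as an alternative cause, can be filed as either

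*Protocol article*

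**What the plan says.** All references are to the protocol article.

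- **Objectives.** The primary safety objective covers "number and severity of acute adverse events, as well as deaths suspected to be related to the intervention".
- **Outcomes.** The matching primary outcome is "to evaluate the antivenom safety profile through laboratory and clinical adverse events", with no causality condition.
- **Design of the Apis study.** The trial is open and non-randomised: "It will include 20 adult individuals, of both sexes, afflicted with multiple stings". There is no untreated group.
- **Adverse event (AE), causal relation.** There are four categories. *Probable* needs well-defined timing and no other possible cause. *Possible* needs well-defined timing, "but there is another possible causal factor". *Remote* means improbable but not ruled out. *Not related* applies when timing is absent or doubtful, "or there exists another factor that may be identified as a causal factor of the reaction".
- **Adverse event (AE), intensity.** Degrees I to III are set by the effect on daily activity; degree III, for example, is "incapacity to work or perform normal daily activity". Degrees IV and V are immediate risk to life and death.
- **Serious adverse event (SAE).** Among the qualifying results is "hospitalization or the prolongation of an existent condition".
- **Symptomatic treatment.** One stated aim is "To treat and prevent hypersensitivity reactions inherent to venom or antivenom", so the article itself recognises two sources for these reactions.

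**The concern.** A causality scale should give each event one category. Here an alternative cause is part of the definition of *possible* and is also enough, by itself, for *not related*. In many trials that overlap would touch a few events. Here the alternative cause is the reason for enrolment: everyone has received venom shortly before the antivenom, and there is no control group to show what venom alone would have done.

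Two investigators following the text faithfully could therefore code the same hypotension or urticaria, or the same death, on opposite sides of the related/not-related line. All centres in a national network are invited, so readings may differ between sites. In a first-in-human study of a heterologous serum, a genuine antivenom reaction should not be validly recordable as *not related*.

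**Working it through.** The article gives no figure on this point, so there is nothing to reproduce. The check is logical, followed by an illustration of size.

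**Step 1. Apply the definitions to every combination of timing and alternative cause.**

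| Timing | Other possible cause | Categories met |
|---|---|---|
| Well defined | No | *Probable* |
| Well defined | Yes | *Possible* and *not related* |
| Absent or doubtful | No | *Not related* |
| Absent or doubtful | Yes | *Not related* |

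*Remote* is left out because its definition uses neither timing nor alternative cause. For the same reason it cannot break the tie in the second row.

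**Step 2. See which row this population occupies.** The Background lists flushing, urticarial plaques, hypotension, tachycardia and bronchospasm among the effects of multiple stings. The Risks and benefits section names acute hypersensitivity to heterologous serum as a risk of the product. A reaction of this kind during or soon after infusion has well-defined timing, and venom is another possible cause. It falls in the second row.

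**Step 3. Trace which results use the classification.**

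- Deaths suspected to be related (primary objective): affected.
- Any tabulation of related events: affected.
- Number of all adverse events: not affected. The AE section counts events whether or not they are considered related, and its Observation paragraph counts any unfavourable sign after administration.
- SAE reporting to the coordinating centre within 24 h: not affected, because it carries no causality condition.

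**Step 4. Size.** Assume *k* of the 20 participants have a second-row event. The related proportion is *k*/20 if all are coded *possible* and 0/20 if all are coded *not related*. One participant is 1/20 = 5 percentage points. Exact (Clopper–Pearson) 95% limits are the 2.5% quantile of Beta(*k*, 21 − *k*) and the 97.5% quantile of Beta(*k* + 1, 20 − *k*). For *k* = 0 the lower limit is 0 and the upper is 1 − 0.025^(1/20) = 16.8%.

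| *k* | All coded *not related* | All coded *possible* |
|---|---|---|
| 2 | 0/20 (0–16.8%) | 10% (1.2–31.7%) |
| 5 | 0/20 (0–16.8%) | 25% (8.7–49.1%) |
| 10 | 0/20 (0–16.8%) | 50% (27.2–72.8%) |

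These are the extremes. Mixed coding gives values in between. *k* is an assumption, as the article gives no expected reaction rate.

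**Step 5. Secondary wording.** Participants are already inpatients when adverse event recording starts. Read literally, the SAE list does not name prolongation of the current hospital stay; it names prolongation of a condition. For intensity, all treated patients must be in hospital during infusion, so an activity-based scale separates degrees I to III poorly in the period when acute reactions occur.

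**The case against.** The best defence of the categories is that *possible* refers to a suspected alternative cause and *not related* to an identified one. That is probably what was intended. The text does not secure it, because the *not related* clause speaks of a factor that *may* be identified as causal, and venom always meets that condition here. It is also fair to say that *probable* being rarely usable is no error: the article reserves it for near-certain relations.

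Several stronger readings are tempting but are not supported:

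- *The primary safety outcome as a whole will be misclassified.* In the objective, the words on suspected relation qualify deaths, and the outcome has no causality filter. The all-cause count stands. What the text shows is that events cannot be uniquely classified, not that they will be classified wrongly.
- *Slowly resolving envenomation will inflate the SAE count.* Conditions present before administration are recorded as medical history, a pre-existing condition becomes an AE only if it worsens, and an SAE must first be an AE. Envenomation that resolves slowly without worsening is neither.
- *The intensity scale is unusable.* Degrees IV and V do not rest on daily activity, and degrees I to III still work at the visits 10, 20 and 30 days after discharge.
- *Laboratory grading is missing.* A condensed article may leave such thresholds to the full protocol.

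The related proportion in the illustration is likewise not an endpoint that the article names.

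**Conclusion.** The concern holds for the causality categories. As written, a well-timed event with another possible cause is both *possible* and *not related*, and in this population that describes most acute reactions and any death for which venom is a plausible alternative. The defect reaches one causality-dependent part of the primary objective, suspected-related deaths, and any related-event table. It leaves the all-cause adverse event count intact.

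Each participant reassigned moves a related proportion by 5 percentage points; the wider ranges above depend on the assumed number of such events and on uniform coding at one extreme. The conclusion rests on the printed definitions being those the sites use. The seriousness phrase and the activity-based degrees I to III are secondary wording defects.

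**What to change.** 1. Define *not related* as no plausible temporal relation to the antivenom, or another cause that is established and sufficient to exclude it.
2. State that an event compatible with both venom and antivenom is at least *possible*.
3. Make the main safety table all events from the start of infusion, regardless of causality, broken down by time from infusion. The article already counts events regardless of relation. The explicit starting point and the time breakdown are new. Causality tables then become supportive.
4. In the SAE section, replace the prolongation of a condition with prolongation of existing hospitalisation.
5. For events during the hospital stay, grade degrees I to III on clinical criteria instead of daily activity.

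The cost is revised wording in the AE and SAE sections and matching changes to the electronic case report form lists. Events already coded, if any, would need recoding. The downside for the sponsor is that the related-event rate may look less favourable.

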##### Observation

For the current study, an adverse event is considered any unfavorable and unintended signal that occurs after administration of the antivenom against bee stings. Conditions prior to such administrations must be registered as medical history.

#### Serious adverse event (SAE)

A serious adverse event is an AE that occurs during any phase of the study and that meets the following criteria: it threatens life; it results in death or a significant or permanent incapacity, congenital anomaly, hospitalization or the prolongation of an existent condition.

Serious adverse events also should be classified according to the guidelines of the previous item, filled out in the SAE formulary, sent to the coordinating center within 24 h of obtaining the knowledge by means of a virtual study platform and should be reported concomitantly with the system CEP-CONEP. The coordinating center will immediately notify ANVISA and subsequently the Department of Science and Technology in the Ministry of Health (DECIT/SCTIE/MS).

#### Pregnancy

The occurrence of pregnancy during the study will need to be communicated immediately to the coordinating center via a pregnancy report formulary and reported concomitantly to the system CEP-CONEP. For such an occurrence, the participant would need to discontinue participation in the study.

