### Discontinuation

Developing anaphylactic shock resistant to the management protocol for reactions of acute hypersensitivities.Withdrawing from the terms of free and informed consent.

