### Plan of treatment (specific, adjuvant, symptomatic and complementary)

#### Specific treatment

The *WHO Guideline for the production control and regulation of snake antivenom immunoglobulins* [12] suggests that the protocol prepared for the specific treatment be based on the estimated quantity of venom inoculated by the bee and on the neutralizing capacity of the antivenin. Thus, the authors suggested:Up to 5 stings: specific treatment is not indicated, except for a medical criterion.Between 5 and 200 stings: two vials of apilic antivenom.Between 201 and 600 stings: six vials of apilic antivenom.Above 600 stings: ten vials of apilic antivenom.

After the dose is determined by the attending medical team, the vials must be opened and their content aspirated by means of a syringe. Next, insert all the content into a flask containing 250 mL of normal 0.9% saline solution, previously emptied. This flask containing the antivenom must be connected into a Y formation with another flask containing 250 mL of 0.9% saline. One large-caliber vein of the forearm must be catheterized and these two contents need to be infused in the Y within two hours. All patients must be hospitalized and monitored throughout the infusion by the continuous presence of the hospital staff at the patient’s bedside. The team must also have at their disposal the drugs and equipment necessary for the treatment of mild or severe adverse reactions. Any adverse events and signs and symptoms of possible toxicity must be noted on the patient’s chart.

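### Pregnancy ends study participation after a single infusion, and the shock criterion does not say whether the infusion or the follow-up stops

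*Protocol article*

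**What the plan says.** All references are to the protocol article.

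- **Pregnancy.** An occurrence must be "communicated immediately to the coordinating center via a pregnancy report formulary" and reported to the ethics system. The section then states that in such a case "the participant would need to discontinue participation in the study". It mentions no follow-up of the pregnancy's outcome.
- **Discontinuation.** There are two items: "Developing anaphylactic shock resistant to the management protocol for reactions of acute hypersensitivities" and "Withdrawing from the terms of free and informed consent". The text does not say what is discontinued.
- **Specific treatment.** The antivenom and saline are given once: "these two contents need to be infused in the Y within two hours". No repeat dose is described.
- **Objectives.** Safety is primary, including "number and severity of acute adverse events, as well as deaths suspected to be related to the intervention".
- **Table 1.** Assessments fall on Day 1, Day 2, at discharge, and at R1, R2 and R3 (10, 20 and 30 days after discharge). Adverse events, laboratory tests and the pharmacokinetic profile, whose footnote covers antibodies against the antivenom, are marked at every one.
- **Serious adverse event.** Congenital anomaly is among the criteria, and reports go to the coordinating center within 24 h.
- **Risks and benefits.** Delayed hypersensitivity is a named risk.

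**The concern.** In a trial with repeated dosing, a discontinuation rule can protect the participant by stopping further exposure. Here exposure is complete within two hours. A rule that ends participation after that point removes observation and protects no one from further study treatment.

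The pregnancy rule does this explicitly. The shock criterion leaves it open, and in a multicenter trial different sites could settle it differently for the participant with the worst reaction. At stake are the later safety data: the visits after discharge, delayed reactions, antibody measurements and the outcome of a pregnancy exposed to a product that the ANVISA approval section describes as the first bee-sting antivenom evaluated in a human trial. Loss of follow-up triggered by a safety event is also not random, so it cannot be treated as ordinary dropout.

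**Working it through.** The plan gives no figure on this point. The 20 participants are fixed without a sample-size calculation (Design of the *Apis* study), so there is nothing to reproduce. The check is mainly a comparison of sections.

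**Step 1: what the pregnancy rule can stop.** Being pregnant is an exclusion, and Table 1 schedules a pregnancy test on Day 1. The rule therefore reaches only a pregnancy missed at entry, or one starting between entry and 30 days after discharge. Study treatment lasts at most two hours and is not repeated. Unless the pregnancy is discovered during the infusion, what ends is follow-up.

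**Step 2: fit with the safety definitions.** The SAE section counts congenital anomaly among events occurring in any phase of the study. A participant who must leave on becoming pregnant cannot normally reach that criterion within the study. The pregnancy form records the occurrence, and nothing stated records the outcome.

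**Step 3: what the shock criterion can stop.** Shock can arise while the infusion runs, so stopping the infusion is one possible meaning. The neighbouring item, withdrawal of consent, is a study-level exit, so leaving the study is another. The text does not choose between them.

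**Step 4: what study exit would lose.** Table 1 has 6 assessment points. Exit on Day 1 would forgo up to 6 − 1 = 5 of them (Day 2, discharge, R1, R2, R3). Exit at discharge would forgo 3 (R1 to R3). The shock itself would not be lost, because it is life-threatening and so reportable as an SAE within 24 h.

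**Step 5: scale, under assumed counts.** One participant is 1/20 = 5 percentage points. Suppose one participant leaves, is dropped from the denominator, and has a later event that goes unseen. Exact (Clopper-Pearson) 95% limits are:

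- Event missed, 0/19: lower limit 0; upper limit 1 − 0.025^(1/19) = 17.6%.
- Event kept, 1/20 = 5.0%: lower limit 1 − 0.975^(1/20) = 0.1%; the upper limit solves (1 − p)^20 + 20p(1 − p)^19 = 0.025, giving 24.9%.
- For reference, 0/20: upper limit 1 − 0.025^(1/20) = 16.8%.

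Losing one participant hardly changes precision (upper limit 17.6% against 16.8%). Missing one event could change the observed rate from 5% to 0%. This shows how much one participant weighs in a trial of 20. It is not an estimate of what will happen.

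**The case against.** The strongest reply has four parts.

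1. **Study exit after shock is inferred.** The Discontinuation section does not say that follow-up ends. The Specific treatment section provides bedside staff and equipment for severe reactions during the infusion, so stopping the infusion is an equally natural meaning. The abstract's Methods paragraph describes evaluation up to 30 days after discharge without exception. This stands: the shock half supports a finding of ambiguity only.
2. **The primary safety measure is largely protected.** The objective names acute events and suspected related deaths. The shock is reported within 24 h, patients are hospitalized, and death is itself an SAE criterion. This also stands. A reader might infer that the two rules remove the most informative participants and bias the serious-event and death rates downward. The document does not support that. The 0/19 example needs both removal from the denominator and an unreported death, and no section states either.
3. **Pregnancies will be rare.** Pregnancy is excluded and tested for at entry, the window is short, and the 20 adults are of both sexes. This stands as a limit on size and does not defend the rule.
4. **The article is condensed.** Visits after discontinuation and pregnancy-outcome follow-up may be set out in the full protocol. This holds for what the article merely leaves out, but not for the pregnancy sentence, which the article states outright. A full protocol that kept such participants in the study would contradict it.

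**Conclusion.** The point holds in a narrow form. The pregnancy rule, followed as written, ends safety observation with normally no study treatment left to stop. That fits poorly with safety as a primary objective and with congenital anomaly as an SAE criterion. The shock criterion is ambiguous between stopping the infusion and leaving the study. Only the second reading would cost data, and then the later course rather than the shock itself.

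The size is small in expectation: an assumed 0 to 2 participants of 20, each losing up to five scheduled assessments, or three if the exit is at discharge. The conclusion assumes that the single infusion is the whole of study treatment, as described, and that the unseen full protocol does not already say otherwise. Confidence is high for pregnancy and limited for shock. This is an inexpensive improvement and does not put the trial's safety conclusions in doubt.

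**What to change.** In the Discontinuation and Pregnancy sections:

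- Separate stopping the infusion from leaving the study, and say which of the two each criterion refers to.
- State that everyone who received any antivenom stays in the remaining Table 1 safety visits, and in the safety denominator, unless consent is withdrawn.
- State that the outcome of any reported pregnancy is recorded.

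The cost is a change of wording in two sections. The visits are already scheduled. The one addition is pregnancy-outcome follow-up beyond 30 days after discharge, for what should be very few cases. No decision about giving, stopping or managing treatment changes.
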